## Abstract

**Background:**

Endometrial cancer (EC) is the most common gynecological cancer in women globally. It is linked to increasing obesity rates and longer life spans. The molecular mechanisms leading to EC are unclear; however, women with polycystic ovary syndrome (PCOS) have a 3- to 5-fold increased EC risk. According to a pilot study conducted in the United Kingdom, insulin-like growth factor-1 (IGF-1) gene and protein were raised in the endometrium and blood of women with EC and PCOS, compared with those without PCOS (controls). Therefore, raised serum IGF-1 levels may contribute to an increased EC risk in women with PCOS, but it is necessary to test this hypothesis since not all studies have demonstrated this association.

**Objective:**

This study aims to investigate the role of IGF-1 in mediating EC risk in PCOS. This will be achieved by evaluating the proliferative effects of PCOS serum, IGF-1, and IGF-1 antagonist on human endometrial cancer 1-A and 1-B cell lines, with a comparison to controls (using serum from women without PCOS and cell culture media). The study will also identify differentially expressed genes and pathways activated by various treatments.

**Methods:**

We intend to recruit 20 women with PCOS and 20 women without PCOS for this cross-sectional study. All experiments will be carried out 4 times to ensure consistency. We will perform transcriptomic and phosphoproteomic profiling to identify differentially expressed genes and phosphoproteins between different treatments using RNA sequencing and phosphoproteomics. We will also perform bioinformatics pathway analysis to identify whether any unique collection of genes or phosphoproteins explains increased EC risk in PCOS. The primary outcome measure will be the cell proliferation (growth) difference measured by cell index values. Our protocol stands out due to its unique approach; no previous study has used this approach to investigate the oncogenic effect of serum from women with PCOS. Additionally, no previous study has considered the differential mutations of genes related to the insulin signaling pathway across various types of human EC cell lines and the potential impact of these variations on their experimental findings.

**Results:**

Participants are currently being recruited. It is expected that preliminary findings suitable for analysis and publication will be available by the summer of 2024.

**Conclusions:**

Although we currently do not have any results to report, sharing our protocol at this stage will aid in research collaboration, provide an opportunity for early feedback, and help reduce duplication of effort by other research groups. The findings of our study will have broader implications. A deeper understanding of the mechanisms underlying the regulation of the IGF system in PCOS and EC will improve our ability to develop effective treatment modalities for EC and will be a vital step toward reducing EC in women globally.

**International Registered Report Identifier (IRRID):**

DERR1-10.2196/48127

## Introduction

### Overview

Endometrial cancer (EC) was the sixth most diagnosed cancer in women globally, in 2020 [1], with 417,000 new cases and 97,000 deaths. The incidence is also increasing rapidly with rising rates of obesity [2] and longer life expectancy. It is estimated that the incidence will increase by more than 50% worldwide by the year 2040 [1]. EC was also the most common gynecological cancer in the United Arab Emirates in 2020, with a 5-year prevalence of 491 per 100,000 individuals [3]. The most common type of EC is type 1 (endometrioid), which is present in 80% of tumors. Treatment often involves hysterectomy—a major surgical operation with serious implications, such as infertility, for younger women [4], which is of growing concern in the United Arab Emirates [5]. There is, therefore, an urgent need for research to prevent and improve the management of EC in the United Arab Emirates and globally. However, uncertainty persists about the precise molecular mechanisms leading to EC, which hinders facilitating EC prevention and treatment.

Some of the known risk factors for EC include polycystic ovary syndrome (PCOS), diabetes, obesity, inflammation, insulin resistance, high estrogen concentrations, and possibly, high circulating insulin-like growth factor 1 (IGF-1) levels [6]. PCOS is, however, the most common female endocrinopathy [7] in women of reproductive age, and potentially, it could account for many cases of EC. PCOS is associated with obesity, infrequent menstrual periods, infertility, hirsutism, enlarged ovaries with many small follicles on ultrasound imaging, increased risks of type-2 diabetes in later life, and a 3- to 5-fold increased risk of EC [8,9], with higher risks in premenopausal women. Mechanisms thought to increase EC risk in PCOS include raised estrogen levels, obesity, anovulatory menstrual cycles, and unopposed (from progesterone) estrogen stimulation of the endometrium; however, the degree to which these mechanisms increase EC risk or interact with each other to underpin EC risk in PCOS is uncertain [10]. Genomic and proteomic approaches [11] have also identified potential new genes and proteins that might explain the link between PCOS and EC and could upregulate genes associated with the insulin signaling pathway in PCOS.

Over the past few years, research studies have investigated the potential role of insulin resistance and IGF-1 in the association between PCOS and EC [12,13]. The possible role of insulin resistance and IGF-1 in the association between PCOS and EC is supported by observations that endometrial dysfunction, causing miscarriages in PCOS, has been linked to insulin resistance and the associated elevation in serum IGF-1 levels in individuals with PCOS [14]. Epidermal growth factor, IGF-1, and IGF-2 were also found to stimulate a time-dependent mitogenic response in human EC cell lines [15]. The most frequently altered mutation in type 1 EC is the phosphoinositide 3-kinase (PI3K) pathway [16]. Elevated IGF-1 and insulin levels have been shown to directly stimulate cell proliferation by activating the phosphatidylinositol-4,5-bisphosphate 3-kinase catalytic subunit alpha pathway [17]. However, the precise association between serum IGF-1 and EC is still uncertain, and results from case-control studies are conflicting [18]. Multiple other molecular pathways also contribute to EC progression. Dysfunction in the TP53 pathway is common in type 2 EC, resulting in the loss of crucial p53 functions. Additionally, the overactivation of the mitogen-activated protein or extracellular signal-regulated kinase (ERK) pathway promotes EC cell proliferation and migration. These pathways, however, interact with IGF-1 signaling, and IGF-1 gene promoter polymorphisms are associated with EC [18].

The importance of investigating the IGF-1 pathway in the association between EC and PCOS is justified. This is because EC is a disease mainly driven by phosphoinositide 3-kinase (PI3K), as the PI3K pathway is aberrant in more than 90% of ECs. PI3K signaling is the main pathway cascade of insulin or IGF-1 signaling [19].

### Prior Work

In a pilot study in which 102 women were recruited, the investigators found for the first time that IGF-1 gene and protein levels were raised in the endometrium and serum of women with PCOS and EC, compared with controls. These two groups exhibited similar levels of obesity [13]. Raised serum IGF-1 levels may, therefore, contribute to an increased risk of EC in women with PCOS; however, there is a need to test this hypothesis since not all studies have demonstrated an association between serum IGF-1, IGF-binding protein 1, IGF-binding protein 3, and insulin levels with EC [20]. A recently published systematic review [21] found that IGF-1 levels in women with PCOS were elevated compared with controls, as found in our pilot study. A total of 20 studies were included in the meta-analysis [21] involving 657 individuals: 362 patients with PCOS and 295 normal controls. The results of the meta-analysis showed that serum IGF-1 levels were significantly higher in patients with PCOS compared to controls (standard mean difference 0.89). Subgroup analysis based on BMI showed that elevated IGF-1 levels were associated with normal-weight and overweight patients in the PCOS group. Further clarification is required about the interplay between PCOS, IGF-1, and the endometrium as well as the impact they have on EC.

### Aims

The aim of this study is to further investigate the possible role of IGF-1 in mediating the risk of EC in women with PCOS.

### Objectives

The objectives of the study are as follows:

To compare the oncogenic effect of PCOS serum, IGF-1, and IGF-1 antagonist on EC cell lines in women with PCOS and controls (using serum from women without PCOS and cell culture media)To identify differentially expressed genes and pathways activated by different treatments used in the previous objectivePerform a bioinformatics pathway analysis to identify whether any unique genes or nodes can explain the increased EC risk in PCOS

Although using cell culture experiments, as described in this paper, is not a novel approach for studying molecular mechanisms to help the prevention and treatment of diseases [22], the unique aspects of our protocol lie in the fact that no previous study has used this approach to investigate the oncogenic effect of serum from women with PCOS. More importantly, no previous study has considered the differential mutations of genes related to the insulin signaling pathway in human endometrial cell lines, as identified in the Cancer Dependency Map Portal [23], and what impact this may have on their experimental findings (Figure 1).

**Figure 1 figure1:**
[figure not shown]
Comparing the oncogenic effect of polycystic ovary syndrome (PCOS) serum on endometrial cancer cell lines with the effect of serum from women without PCOS (controls) and insulin-like growth factor 1 (IGF-1).

## Methods

### Ethics Approval

Ethics approval for this study has been obtained from the research ethics committees of Mohammed Bin Rashid University of Medicine and Health Sciences (MBRU IRB-2022-149) and Kings College London in Dubai (October 12, 2022). Approvals from other hospital sites (Latifa Women and Children’s Hospital and Mediclinic Hospitals in Dubai) will be sought, as appropriate, based on participant recruitment rates.

### Recruitment

The study will aim to recruit 20 women with PCOS and 20 women without PCOS aged between 18 and 45 years. We will recruit women with PCOS and controls into the study if they have a BMI below 30 and are not on any medications. This is to mitigate the possible confounding effect of obesity on EC risk. Inclusion criteria for women with PCOS will involve a diagnosis using the Rotterdam Criteria [24], which encompasses the presence of 2 or more of the following conditions: clinical or biochemical evidence of hyperandrogenism, chronic oligo-ovulation or anovulation, and the observation of polycystic ovaries on ultrasound, with the exclusion of other causes of chronic oligo-ovulation or anovulation (eg, hyperprolactinemia and hyperthyroidism). Controls will be women with regular menstrual cycles identified from a gynecology or other appropriate outpatient setting at Kings College Hospital, Latifa Women and Children’s Hospital, or Mediclinic Hospital in Dubai, without a diagnosis of polycystic ovaries on ultrasound scan. Male patients will be excluded from this study, as they do not develop EC.

Women identified as having PCOS or controls will be identified by gynecologists in participating hospitals and provided a patient information sheet. If the patient agrees to participate, written consent will be obtained. One of the study investigators will then be informed by the clinician or gynecologist who recruited the patient into the study. The investigator will then contact the participant to arrange a mutually convenient time for sample collection. For women with and without PCOS recruited into the study, participation will not involve any extra visits to the hospital in addition to visits required as part of their clinical care. Fasting blood samples will be obtained following the exclusion of a possible pregnancy. With the permission of the participants, we will review their electronic medical records to obtain details on their medical and gynecological history, including the reason for clinical presentation, menstrual history, date of last menstrual period before sample collection, past medical or surgical history, medication, allergies, and smoking history. The most recent height, weight, and blood pressure measurements in the electronic medical record will be recorded. The details of their last pelvic ultrasound scan will also be recorded to confirm if their ovaries did or did not look polycystic.

Participants can withdraw from the study at any stage without their clinical care being affected. We do not anticipate any issues with adverse effects; however, the research team aims to meet fortnightly as a research group during the study, with steering committee meetings arranged as indicated. The principal investigator will report any relevant data safety issues reported during these meetings or from any other sources to the Mohammed Bin Rashid University’s Institutional Review Board (IRB).

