The primary outcome measure will be the difference in cell proliferation measured by cell index values during the xCELLigence real-time cell proliferation experiment. Comparison of cell index values from cells treated in different groups will be performed by the Kruskal-Wallis test followed by multiple comparison tests.

### Objective 2: Identifying Differentially Expressed Genes and Pathways Activated by the Treatment of Endometrial Cell Lines of the Different Study Groups Listed in Objective 1

We will perform transcriptomic profiling of endometrial cell lines to identify differentially expressed genes in response to different study conditions outlined previously, using RNA Sequencing (RNA-Seq) to identify the molecular targets and pathways involved in the oncogenic effects (Figure 3).

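### The PCOS v control serum comparison relies on restriction at entry alone: no matching or adjustment is described, and the named Kruskal-Wallis test cannot use age or BMI

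*Protocol article*

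**What the plan says.** All of the design statements are in the Recruitment section of the protocol article.

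- **Size and age range:** "The study will aim to recruit 20 women with PCOS and 20 women without PCOS aged between 18 and 45 years".
- **Restriction:** women in both groups are eligible "if they have a BMI below 30 and are not on any medications". The stated purpose is "This is to mitigate the possible confounding effect of obesity on EC risk".
- **Controls:** "Controls will be women with regular menstrual cycles identified from a gynecology or other appropriate outpatient setting". No matching criterion is given.
- **Sampling:** samples are fasting and taken after pregnancy is excluded, on a day that suits the participant and without extra hospital visits. The day is not tied to the menstrual cycle.
- **Data held:** "The most recent height, weight, and blood pressure measurements in the electronic medical record will be recorded". The record review also covers "date of last menstrual period before sample collection". Age is known from eligibility.

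The primary analysis is at the end of the section on endometrial carcinoma cell lines, under Objective 1. The comparison of cell index values between treatment groups "will be performed by the Kruskal-Wallis test", followed by multiple comparison tests. No other analysis of the primary outcome is named.

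**The concern.** Restriction narrows a confounder; it does not balance it. The cap removes obese women from both groups but leaves the whole range below 30 open. The Introduction says that PCOS is associated with obesity, so eligible women with PCOS may on average sit higher in that range than eligible controls. Age may also differ between a PCOS group and a general outpatient control group, since the only limit is 18-45.

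The plan treats obesity as a confounder, yet it names a test with no place for BMI or age, although both are already held. If either is related to how strongly a woman's serum drives proliferation, part or all of a PCOS v control difference in cell index could belong to that trait and be credited to PCOS. This concerns the between-woman comparison of PCOS serum with control serum, which is central to Objective 1.

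**Working it through.** **No stated figure to reproduce.** The article gives 20 per group without alpha, power, effect size or SD for cell index.

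**1. Bias from an unadjusted covariate**

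Inputs from the article: 20 women per group. Assumed: two-sided 5% test, one value per woman, a t test standing in for the rank test, a systematic gap *s* between groups in one covariate (within-group SD units), and a within-group correlation *r* of that covariate with cell index.

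- Bias in outcome SD units: *b* = *s* × *r*
- Standard error of the group difference: √(2/20) = 0.316 SD
- Noncentrality: *b* / 0.316 = *b* × √10
- Degrees of freedom: 40 − 2 = 38; critical t = 2.024

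| Gap *s* | Correlation *r* | Bias *b* | Noncentrality | Rejection rate with no PCOS effect |
|---|---|---|---|---|
| 0.3 | 0.2 | 0.06 | 0.19 | 5.4% |
| 0.5 | 0.3 | 0.15 | 0.47 | 7.5% |
| 0.8 | 0.3 | 0.24 | 0.76 | 11.5% |
| 0.8 | 0.4 | 0.32 | 1.01 | 16.7% |

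**2. Cost of adjusting for age and BMI**

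Two covariates leave 38 − 2 = 36 df (critical t = 2.028). The squared standard error becomes (2/20) × (1 − R²y)/(1 − R²x). R²x is the share of group status that the covariates explain; R²y is the share of within-group outcome variance that they explain. For illustration I use a difference of 0.89 SD. That is the article's meta-analytic difference for serum IGF-1, and carrying it over to cell index is an assumption.

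- Unadjusted: noncentrality 0.89 × √10 = 2.81, power 78.3%.
- Adjusted, R²x = R²y = 0 (degrees of freedom only): 78.2%.
- Adjusted, R²x = 0, R²y = 0.2: 86.5%.
- Adjusted, R²x = 0.2, R²y = 0: 68.8%.
- Adjusted, R²x = 0.5, R²y = 0: 49.1%.
- Where R²x = R²y the two factors cancel: 78.2%.

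For a single covariate in equal groups, R²x = *s*²/(4 + *s*²). A gap of 0.8 SD gives 0.64/4.64 = 0.14, 1 SD gives 1/5 = 0.20, and 2 SD gives 4/8 = 0.50. The heaviest loss therefore needs a gap well beyond the range used in step 1.

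**3. Which contrasts are exposed**

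The plate design tests each woman's serum alone, with IGF-1, with inhibitor, and with both. In a difference between two conditions on the same serum, an additive effect of that woman's age or BMI appears in both terms and cancels. In PCOS serum minus control serum the terms come from different women, and nothing cancels.

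**The case against.** The best defence is that a journal article is a condensed account. Covariate sets and sensitivity analyses are commonly left to a full protocol or analysis plan, which is not shown, so the absence of an adjusted analysis proves little. That stands as far as it goes. What remains is that the article does fix a primary test, and that test cannot adjust.

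Several stronger readings are tempting, and the documents do not support them.

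- **That the BMI cap is the only safeguard.** It is not: no medication, age 18-45, fasting and exclusion of pregnancy also apply. None of these balances BMI or age between groups.
- **That adjustment is free.** The data and the degrees of freedom cost almost nothing, but covariates that track PCOS status without affecting cell index widen the standard error, as step 2 shows.
- **That cycle timing should be a covariate.** Oligo-ovulation or anovulation is one of the Rotterdam criteria, and unopposed estrogen is listed as a mechanism for the excess cancer risk. Adjusting could remove part of the effect under study. Days since the last period also mean different things in regularly cycling and oligo-ovulatory women.
- **That the article shows IGF-1 varying with BMI below 30.** The Prior Work section reports that "elevated IGF-1 levels were associated with normal-weight and overweight patients in the PCOS group". That places a PCOS v control difference in those weight groups; it says nothing of a gradient with BMI within them.
- **That chance imbalance at 20 v 20 inflates the error rate.** Unconditionally it does not, because chance variation is already in the within-group variance. Only a systematic gap biases the test.
- **That the IGF-1 contrasts are confounded too.** Within one serum, additive traits cancel.

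**Conclusion.** The point holds for the between-woman comparison of PCOS with control serum, and it is worth changing the plan for. Beyond restriction at entry, no balancing or adjustment is described, and the named test cannot supply it.

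The size is uncertain. A rejection rate of about 5% to 17% at a nominal 5% rests wholly on assumed gaps (0.3-0.8 SD) and correlations (0.2-0.4). Much of that range is modest, and the top figure is its extreme corner. The direction for BMI is an inference from the article's statement that PCOS goes with obesity; for age the documents give no evidence of a systematic gap, only room for one. An unseen analysis plan may already contain an adjusted analysis, but it would have to replace or supplement the test named here.

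**What to change.** 1. Summarise cell index to one value per woman per condition, or use a mixed model with woman as a random effect. Estimate PCOS v control serum adjusted for age and BMI, both continuous.
2. Keep the unadjusted rank test as a supporting analysis.
3. Where feasible, frequency-match the remaining controls to the women with PCOS on age band and BMI (below 25, 25-29.9). The article reports 2 controls recruited, so 20 − 2 = 18 were still to come, and data analysis had not begun.
4. Report cycle timing descriptively by group and do not adjust for it.

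**Cost:** 2 of 38 degrees of freedom; some loss of precision if age or BMI tracks PCOS status without affecting cell index; slightly slower control recruitment if matched. No new data are needed. One limit remains: BMI comes from the latest values in the medical record, not from a measurement at sampling, so adjustment will be somewhat incomplete.

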### Blood Tests

Following informed consent, 1 extra sample of blood (in addition to the other blood tests required as part of their clinical care) will be obtained from the participant’s arm and collected into 1 vacutainer for the study. Whole blood collected from patients with PCOS and controls will be stored for a maximum of 24 hours before the serum is separated. Samples will be transported from the gynecology clinic to the laboratory at Mohammed Bin Rashid University, ideally within 6 hours of whole blood collection, in dry ice between 2˚C and 8˚C, with the tubes stored in specimen bags.

We anticipate no major problems with side effects; nonetheless, following the blood tests, the participants may experience minor bruising in the area from which blood was obtained. However, all the blood tests will be taken by an experienced staff member, which should help minimize this risk. Participants will be informed that during the cell culture studies, we may identify incidental factors that might be associated with an increased risk of EC. Should this occur, the results will be made available to participants and their general practitioners or family medicine doctors if they so wish, and they will be offered appropriate counseling. They will also be informed that we may not find any significant differences between blood samples taken from women with PCOS and controls and that there will be a need for further studies on more women to confirm any of our findings. The experiments will not involve any techniques that will put staff at risk or produce environmental contaminants. Participants will also be informed that the potential benefits are that this study might identify new genetic or chemical factors that may prove significant in future studies for the prevention and treatment of EC and that this will be a vital step in reducing the incidence of EC in women living in the United Arab Emirates.

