### Processing and Storage of Blood Samples

Whole blood will be allowed to clot for 15-30 minutes at room temperature or left at 4˚C until the reaction is complete. We will aim not to exceed 24 hours and isolate serum within 1 or 2 hours of blood collection. Once the blood has been clotted, it will be centrifuged at 1000 x gravitational units (g) for 10 minutes in a refrigerated centrifuge (at 4˚C) to facilitate the separation of the serum. A barrier will form between the serum and the cells; if no barrier is formed, the sample will be respun for 5 minutes. The serum will be carefully extracted using a fine-bore pipette to prevent the inclusion of red blood cells and will be aseptically transferred to a sterile vial. The samples will be kept at temperatures ranging from 2°C to 8°C during handling. The serum will then be stored without delay at –80˚C in 0.5 mL aliquots to prevent the disintegration of serum proteins. Upon completion of the initial studies with the blood tests obtained from the participants, with their consent, we will retain some of the remaining serum samples for long-term storage to allow further studies if newer technology for carrying out these studies becomes available. However, if participants do not wish to have their serum samples retained for this part of the study, the sample will be discarded in accordance with the established laboratory protocols immediately after the cell culture study. Permission will be sought from the research and ethics committee prior to conducting any further studies using the stored blood samples.

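### Blood samples are to travel on dry ice and at 2–8 °C at once, and the 6 h transport ideal does not fit the aim of isolating serum within 1–2 h

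*Protocol article*

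**What the plan says.** Two adjacent sections of the protocol article's Methods govern the blood samples.

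**Blood Tests.** Whole blood from both groups "will be stored for a maximum of 24 hours before the serum is separated". The samples then go from the gynecology clinic to the university laboratory, "ideally within 6 hours of whole blood collection, in dry ice between" 2 °C and 8 °C. The transport condition in full is "in dry ice between 2˚C and 8˚C".

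**Processing and Storage of Blood Samples.** Clotting comes first: "Whole blood will be allowed to clot for 15-30 minutes at room temperature or left at" 4 °C until complete. On time, the section says: "We will aim not to exceed 24 hours and isolate serum within 1 or 2 hours of blood collection". The clotted blood is spun for 10 minutes in a centrifuge at 4 °C. On handling it says "The samples will be kept at temperatures ranging from" 2 °C to 8 °C. Separated serum is then frozen at −80 °C straight away, "to prevent the disintegration of serum proteins".

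**The concern.** The transport instruction names a coolant and a temperature range that exclude each other. Someone packing the box has to ignore one of them, and the article does not say which.

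The choice matters because of what is in the box. Blood Tests speaks of whole blood held before separation, then of transport; clotting and centrifugation appear only in the next section. On the natural reading the tubes shipped still contain cells. Whole blood on dry ice freezes, its red cells lyse, and serum spun off after thawing carries their contents. The authors plainly want to avoid this: they draw the serum off with a fine pipette to keep red cells out, and they freeze it only after separation.

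Participant serum defines the PCOS-versus-control contrast for the primary outcome, cell index, and the same treatment groups feed the RNA sequencing and the phosphoproteomics. One tube is drawn per woman for the study, so the article provides no second sample. Quadruplicate wells do not help either: all four wells receive the same woman's serum, so damage to it is repeated and not averaged away.

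The times raise a second, lesser question: whether a sample that meets the transport ideal can also meet the serum-isolation aim.

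**Working it through.** No sample size, power or error rate is at issue. The check sets the stated temperatures and times side by side.

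**Temperature.** Inputs: stated range 2 °C to 8 °C (Blood Tests); dry ice about −78 °C (general physical fact, not in the article).

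- Gap to the lower end: 2 − (−78) = 80 °C.
- Gap to the upper end: 8 − (−78) = 86 °C.

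Both instructions cannot hold for one sample. The later steps show which kind of blood the plan needs:

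| Step (Processing and Storage) | Stated condition | Needs unfrozen blood? |
|---|---|---|
| Clotting | room temperature, or 4 °C | yes |
| Centrifugation | 4 °C | yes |
| Handling | 2–8 °C | yes |
| Storage of separated serum | −80 °C | no, serum only |

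**Time.** Inputs: arrival ideally within 6 h of collection and a 24 h ceiling (Blood Tests); serum isolated within 1 or 2 h of collection, clotting 15–30 min at room temperature, spin 10 min (Processing and Storage). Assumption: separation happens at the laboratory, after transport.

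Latest arrival that meets the aim = aim − spin − any clotting still to be done.

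- Clotting complete on arrival: 120 − 10 = 110 min for the 2 h aim; 60 − 10 = 50 min for the 1 h aim.
- Clotting at the laboratory: 120 − 10 − 15 = 95 min down to 120 − 10 − 30 = 80 min for the 2 h aim; 60 − 10 − 15 = 35 min down to 60 − 10 − 30 = 20 min for the 1 h aim.
- Arrival at 6 h: serum at the earliest at 6 h 10 min, which is 4 h 10 min beyond the 2 h aim.

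So every arrival between 2 h and 6 h satisfies the transport ideal and misses the isolation aim. The 6 h figure is an ideal and the 1–2 h figure an aim, so the only firm limit is 24 h. That is 24/2 = 12 to 24/1 = 24 times the aim, and 24/6 = 4 times the transport ideal. These ratios compare a ceiling with targets. They show how loose the specification is, not how long actual delays are.

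**Reach.** The list under Endometrial Carcinoma Cell Lines has 12 conditions: 4 with PCOS serum, 4 with control serum and 4 with culture media only. Participant serum enters 4 + 4 = 8 of 12. In the pilot plate of Table 1 it enters 5 women × 4 conditions × 4 wells = 80 of 96 wells; media fill the other 4 × 4 = 16.

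**The case against.** The best defence is that dry ice is a slip of the pen. The same phrase gives 2–8 °C, the next section repeats that range, and clotting and the 4 °C spin need liquid blood. A laboratory reading the whole text would probably ship chilled, and nothing would freeze. This is likely what the authors meant, and it makes the repair easy. It does not make the instruction safe: the coolant is named explicitly, and the person packing the tube need not be the person who processes it.

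On timing, the defence partly succeeds. The 24 h and 1–2 h figures stand in one sentence as a ceiling and a target, and they can coexist. The 6 h figure is an upper bound; all named sites are in Dubai, and trips may be shorter. The clash needs transport beyond about 2 h and separation after transport, and the article does not state outright where separation takes place. What stands is the conflict for late-arriving samples and the unstated place of separation.

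A reader might go further and infer that delay differs between PCOS and control samples and so creates a false group difference. Controls may come from other outpatient settings and several hospitals, so this is possible. But the article sets one 24 h limit for both groups, has gynecologists identify both, and reports that all five women so far came from one hospital. Nothing shows that delay follows group.

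Nor can an inflated error rate be attached. If one assumed a 0.5 SD group difference in delay and a correlation of 0.3–0.5 with growth, the bias would be 0.5 × 0.3 = 0.15 to 0.5 × 0.5 = 0.25 SD, and a 5% t test at 20 versus 20 would reject in about 7.5–12%. Neither input is in the article, smaller values are equally open, and the plan specifies a Kruskal-Wallis test across treatment groups.

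Finally, a sample-time log missing from a journal article is not a defect in itself; such logs usually sit in laboratory procedures.

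**Conclusion.** The transport instruction is wrong as written and has to be corrected. The two conditions lie about 80 °C apart, and following the dry-ice part would damage the serum behind 8 of the 12 conditions. This rests on the physical temperature of dry ice and on the natural reading that whole blood is shipped before separation.

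The timing point is real but smaller. The transport ideal and the isolation aim conflict for samples arriving 2–6 h after collection, provided separation follows transport. It is a loose specification with one firm limit, not three rival rules.

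Unequal handling of the groups remains a possibility that the plan should guard against. It is not a demonstrated bias, and no size can be given for it from the article.

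**What to change.** Reconcile Blood Tests with Processing and Storage of Blood Samples:

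1. Remove dry ice for whole blood, so that transport agrees with the 2–8 °C handling, clotting and 4 °C spin that follow.
2. State where serum is separated: at the clinic or at the university laboratory.
3. Replace the mix of aim, ideal and ceiling with one maximum time from collection to centrifugation that the route can meet, applied identically to PCOS and control samples.
4. Record collection and spin times for each sample, so that delay can be compared between groups.

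The cost is wording and two times per sample. The article reports three women with PCOS and two controls recruited, a second hospital site approved and analysis not yet begun, so the change comes early. The sponsor should check how any samples already taken were shipped. If any were frozen as whole blood, replacing them has to be squared with the undertaking that participation needs no extra hospital visits.
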